With advances in cancer treatment over the decades, the survival time of older patients with cancer has been gradually extended, and the accompanying symptoms of chemobrain have gradually drawn increasing attention [5]. Recent data have shown that chemobrain-related stress could persist for a long-term period after a systemic therapy, which is particularly relevant to older patients with cancer [6]. These individuals report chemobrain symptoms of anxiety and depressive disorder, and the number of older patients with cancer will increase dramatically in the coming future. Although data on cognitive impairment onset after chemotherapy are lacking for older patients with cancer in China, clinical practitioners have paid constant attention to the health of their constituents, given their propensity for worse physical and mental health outcomes related to chemotherapy [7]. Data suggest that up to two-thirds of older patients with cancer develop chemobrain during or after chemotherapy [8]. Most of these patients experience cognitive impairments for months, but 10%-20% of these individuals experience persistent chemobrain-related stress even after many years of completing chemotherapy. In recent years, the incidence rate of cancer in senile patients has been rising in China [9]. The problem of chemotherapy-induced cognitive dysfunction is becoming increasingly common, and there are growing concerns that chemobrain could become a threat. Therefore, it is crucial to explore an intervention that can effectively prevent and treat chemotherapy-induced cognitive impairment in older patients with tumors.

Pre-existing studies [10] have shown that some neuroprotective factors such as methylphenidate and modafinil are effective for treating chemotherapy-related cognitive impairment; however, most clinical trials on interventions for chemobrain report less access to control groups and less treatment engagement. Combo acupoint stimulation therapy is a new technique based on the theory of traditional Chinese medicine and modern biological principles. With the help of invasive or noninvasive interventions, different stimuli or drug intakes would be administered at acupuncture points, meridians, or related specific body surface sites [11].

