Acupuncture has been used for thousands of years in China and other Asian countries to treat various diseases, including sleep disturbance [12]. It is a nonpharmacological therapy that involves inserting needles into acupuncture points and sometimes applying minielectrical current stimulation on acupuncture points via needles or applying acupressure on the surface of points in different parts of the body, including ear and scalp [12]. Electroacupuncture (EA) is an effective family member of combo acupoint stimulation [13]. Lyu et al [14] reported that EA could be effective in alleviating various side effects caused by anticancer drugs, such as pain, vomiting, fever, fatigue, dry mouth, anxiety, depression, and insomnia. In addition, EA could promote the rehabilitation of pathological microstructures in the brain and improve the cognitive ability of patients with cognitive impairment. Clinical trials [14,15] of acupuncture for preventing and managing mild cognitive impairment in older adults show that it can improve the clinical efficacy rate, Mini-Mental State Examination Scale score, Montreal Cognitive Assessment (MoCA) test score, and clock drawing task scores, suggesting that acupuncture can be an effective approach complementary to existing therapies. Evidences [14] from acupuncture in patients after an ischemic stroke support its role in the treatment of neurological deficits through modulation of neuroplasticity. Chemobrain affects cognitive function, in particular, think and memory functions through various mechanisms, including inflammation and oxidative stress, which may lead to neurogenesis and glycogenesis reduction. This pathological process shares some similarities with brain damage after an ischemic stroke [3,16]. Therefore, it is important to investigate if EA is effective in preventing and treating chemobrain in older patients with cancer and for improving the QoL of cancer survivors.

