### Inclusion and Exclusion Criteria

The participants in this study are 168 older patients with cancer who are further assessed for eligibility and meet the following eligibility criteria: (1) have clinically pathological diagnosis of malignant tumor, (2) aged 60 years or older, and (3) are currently undergoing or just about to commence a comprehensive treatment of chemotherapy. The exclusion criteria are as follows: (1) undergone chemotherapy within the last 2 years; (2) metal device or pacemaker planted in the body, developed epilepsy, and experienced instability; (3) participated in a drug trial within the last 6 months; (4) alcohol or drug abuse history in the past year; and (5) those who are afraid of acupuncture.

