## Discussion

Patients with cancer may have concerns of psychiatric and digestive symptoms while undergoing or just after having recently undergone chemotherapy [3]. The most common clinical manifestations are fatigue, nausea, vomiting, dry mouth, anxiety, depression, and insomnia. More seriously, cognitive impairments with a range of neurocognitive symptoms occur frequently, including visual and verbal memory impairment, forgetfulness, difficulty concentrating, learning difficulties, and organizational and coordination dysfunction [3,4]. Since the 1980s, researchers have been studying chemotherapy-induced cognitive impairment and have given several definitions to this condition, such as postchemotherapy cognitive impairment and chemotherapy-induced cognitive dysfunction. Recently, this condition was termed as chemobrain [3-5].

Chemobrain is a frequent side effect experienced by an increasing number of older patients with cancer, and it has significantly impacted their QoL [4]. Chemobrain can be described as cognitive symptoms reported by patients with cancer in self-reported questionnaires or as cognitive changes evaluated by formal neuropsychological tests [5]. Older patients with cancer will experience cognitive impairment due to chemoradiotherapy, which will lead to a series of neurocognitive symptoms called chemobrain. Older populations have been disproportionately affected by chemobrain and have heightened negative mental health outcomes after cytotoxic chemical drug therapy [3,5,7].

According to available literature [3,14], more than 75% of patients with cancer experience cognitive impairment while undergoing chemotherapy or just after completing chemotherapy, with 15%-30% of these patients experiencing persistent symptoms for up to decades. The prevalence of postchemotherapy cognitive impairment is as high as 50%-75% among older cancer survivors [33]. In some circumstances, the cognitive impairment can be lifelong, affecting the patient’s mood, relationships, QoL, career, social activity, and family life. Considering the increasing incidence of cancer, chemobrain is quite complicated, increasingly important, and has far-reaching consequences. As the incidence of cancer survivors rises, the adverse effects of chemobrain will become more frequent, thus necessitating the need to effectively prevent and treat chemobrain.

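### The exclusion list leaves the main non-chemotherapy causes of cognitive impairment in the trial, and exclusion 1 cannot be applied alongside inclusion 3

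*Protocol article*

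**What the plan says.** Inclusion and Exclusion Criteria gives three inclusions and five exclusions, presented as the complete list.

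- The inclusions are: "have clinically pathological diagnosis of malignant tumor", "aged 60 years or older" and "are currently undergoing or just about to commence a comprehensive treatment of chemotherapy". There is no upper age limit, tumour site restriction or cognitive threshold.
- Exclusion 1 is "undergone chemotherapy within the last 2 years".
- Exclusion 2 is "metal device or pacemaker planted in the body, developed epilepsy, and experienced instability".
- The other three concern recent drug trials, alcohol or drug abuse in the past year, and fear of acupuncture.

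The Abstract describes the participants as having clinically confirmed chemobrain. Participants and Recruitment lists such confirmation among the items on the initial screener. Statistical Analyses defines cognitive impairment by a 1.5 SD rule on MoCA and QLQ-C30 scores, and compares its cumulative incidence over 8 weeks between the arms by Kaplan-Meier analysis.

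**The concern.** The conclusion the trial wants to draw concerns impairment caused by chemotherapy. In people of 60 and over with cancer, a low MoCA score has several other common explanations, and the eligibility list deals with very few of them. If such patients enter, their deficit is read as chemobrain. They may then be counted as cases the intervention could not have prevented, or, if they improve, as evidence that it relieves chemobrain. In either case the enrolled population does not match the claim.

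Exclusion 1 raises a second, separate problem. Read literally, it removes patients whom inclusion 3 is written to admit.

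**Working it through.** **Step 1. Set the competing causes against the list.**

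| Pre-existing cause | Removed by the criteria? |
|---|---|
| Known dementia or other diagnosed cognitive disorder | No |
| Previous stroke with cognitive deficit | No |
| Primary brain tumour or brain metastases | No; inclusion 1 accepts any malignant tumour |
| Previous cranial irradiation | No |
| Epilepsy | Yes, exclusion 2 |
| Alcohol or drug abuse | Past year only, exclusion 4 |

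Exclusion 2 also mentions instability without defining it, so it cannot be relied on to cover the first four rows.

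**Step 2. Look for another filter.**

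- *Clinical confirmation of chemobrain* (Abstract; Participants and Recruitment). It is not among the eligibility criteria and no method is given. It cannot apply to a patient who has never had chemotherapy and is about to start, a group that inclusion 3 admits.
- *Screening scales* (Study Design). Reported cognitive dysfunction is recorded through an anxiety scale and a depression scale. Neither establishes a cause.
- *Outcome definition* (Statistical Analyses). It rests on scores, with no attribution step.
- *Covariates* (Statistical Analyses). Baseline cognition and earlier chemotherapy are not listed.

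None of these closes the gap.

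**Step 3. Exclusion 1 against inclusion 3.** A patient already on chemotherapy meets inclusion 3. The same patient has had chemotherapy within the past 2 years and so also meets exclusion 1. Applied literally, the list admits only patients about to start. How a site resolves this determines who is enrolled.

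**Step 4. Size.** The plan gives no figure for the share of such patients, so there is none to reproduce. The inputs are:

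- Control incidence of 30% and a reduction of 10%-20% (Sample Size Estimation), read here as percentage points.
- 84 per arm with 20% dropout, taken as printed: 84 × 0.8 = 67 completers per arm. How 84 was derived is a separate question.
- q, the share of participants with a fixed deficit from another cause. This is **assumed**.

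If these patients count as cases in both arms, the incidence in each arm becomes p′ = (1 − q)p + q, and the difference becomes (1 − q)(p1 − p2). Power uses the normal approximation, two-sided 5%, n = 67 per arm, with p̄ the mean of the two incidences:

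Φ{ [ |p1 − p2| − 1.96·√(2p̄(1 − p̄)/n) ] / √( [p1(1 − p1) + p2(1 − p2)]/n ) }

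At the favourable end of the plan's range, 30% versus 10%:

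| q (assumed) | Incidence by arm | Difference (points) | Power |
|---|---|---|---|
| 0 | 30% vs 10% | 20 | 83% |
| 5% | 33.5% vs 14.5% | 19 | 74% |
| 10% | 37% vs 19% | 18 | 64% |
| 20% | 44% vs 28% | 16 | 49% |

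For q = 0: p̄ = 0.20, 1.96·√(0.32/67) = 0.135, √(0.30/67) = 0.067, and Φ(0.96) = 83%. Power falls faster than the difference because the added cases also move both incidences towards 50%, where the variance is larger.

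These losses belong to the incidence comparison only. In the analysis of MoCA change, a stable deficit largely cancels against the patient's own baseline, so the loss there should be smaller.

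**The case against.** Five points can be made on the other side.

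1. *Broad eligibility is a legitimate choice, and the article condenses a fuller protocol.* This stands in part. However, the list is presented as the criteria rather than as a selection, and it is what a reader or site would apply.
2. *Oncologists screen patients and chemobrain is clinically confirmed.* This would lower q in practice. It does not settle the matter, because confirmation is neither a criterion nor defined, and it is impossible for a chemotherapy-naive patient.
3. *Randomisation spreads such patients evenly.* This stands: no bias between arms follows. Dilution and misattribution remain.
4. *The calculation assumes that patients impaired at baseline count as events.* This also stands. The Kaplan-Meier analysis concerns deficits accumulated over 8 weeks, and the article does not say how baseline impairment is handled. If such patients were left out of the risk set, the difference would not shrink in this way.
5. *The q values are invented.* They are assumptions, shown as a range, and nothing in the article favours any one of them.

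A reader might also infer that the 2-year window contradicts the protocol's own account of how long chemobrain lasts: "10%-20% of these individuals experience persistent chemobrain-related stress even after many years of completing chemotherapy" (Introduction) and "with 15%-30% of these patients experiencing persistent symptoms for up to decades" (Discussion). The text does not support that. Exclusion 1 nowhere says that impairment has cleared by 2 years. The persistence statements concern a minority, and impairment left by an earlier course is still chemotherapy-induced. Nor can those percentages stand in for q: they describe previously treated patients, and the article does not say how many participants that covers.

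**Conclusion.** The point holds in a limited form. The eligibility list does not remove the main pre-existing causes of cognitive impairment, and nothing later in the article separates them from chemobrain. The consequences are dilution of the incidence comparison and doubt about attribution, not bias between arms. The size is unknown because q is unknown. Under the stated assumptions the incidence difference falls by a factor 1 − q, and even q = 5% takes the plan's most favourable scenario below its stated 80% power. The effect on MoCA change should be smaller.

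The clash between exclusion 1 and inclusion 3 rests on the wording alone and needs no assumption.

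A reader might go further and take the Introduction's remark "This pathological process shares some similarities with brain damage after an ischemic stroke" to mean that the MoCA cannot tell stroke from chemobrain. That remark is offered as a reason to try electroacupuncture and says nothing about what the MoCA discriminates. The attribution problem rests on the score-only definition of impairment.

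**What to change.** Add one exclusion to Inclusion and Exclusion Criteria, checked from the existing medical record: dementia or another cognitive disorder diagnosed before chemotherapy, previous stroke with cognitive deficit, primary brain tumour or brain metastases, or previous cranial radiotherapy. Undiagnosed disease will still get through, so this reduces q without bringing it to zero.

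Reconcile exclusion 1 with inclusion 3, for example by stating that exclusion 1 refers to courses before the current one.

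The cost is a protocol amendment and a chart check at screening, with no new procedure. The downside is a somewhat smaller recruitment pool. The article reports 11 of 168 participants recruited by October 21, 2023, so a change at that date would have covered nearly the whole sample. Patients enrolled before the amendment should stay in the main analysis. Their records can be checked for these conditions without knowledge of allocation, and a sensitivity analysis can be run without those affected.

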**Methods:**

This study involves a 2-arm, prospective, randomized, assessor-blinded clinical trial in older patients with cancer experiencing chemobrain-related stress and treated with Chinese acupuncture from September 30, 2023, to December 31, 2025. We will enroll 168 older patients with cancer with clinically confirmed chemobrain. These participants will be recruited through screening by oncologists for Chinese acupuncture therapy and evaluation. Electroacupuncture will be performed by a registered practitioner of Chinese medicine. The electroacupuncture intervention will take about 30 minutes every session (2 sessions per week over 8 weeks). For the experimental group, the acupuncture points are mainly on the head, limbs, and abdomen, with a total of 6 pairs of electrically charged needles on the head, while for the control group, the acupuncture points are mainly on the head and limbs, with only 1 pair of electrically charged needles on the head.

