### Study Design

We present a protocol for a 2-arm, prospective, randomized, assessor-blinded trial to examine the efficacy and safety of EA for chemobrain among older patients with cancer who are undergoing chemotherapy or those are going to just begin chemotherapy. This study refers to a double-blinded trial in which neither the investigator nor the participant knows the group to which the participant belongs (experimental group or control group), and the analyst usually does not know which group the data being analyzed belong to. This study is designed to eliminate subjective biases and personal preferences that may arise in the consciousness of investigators and participants. Those who report clinically significant cognitive impairment are being recruited and enrolled to participate in a trial on the effects of a novel EA intervention to address negative mood symptoms and reduce chemotherapy-induced adverse reactions. Participants are recruited via community organizations, social media, and internet outlets (eg, hospital classified ads, WeChat). Interested older patients with cancer complete a screener assessment by the medical staff of the Oncology department or a Chinese medicine doctor, and they report the levels of cognitive dysfunction they are experiencing through the Overall Anxiety Severity and Impairment Scale [20] and the Overall Depression Severity and Impairment Scale [21]. Those eligible at the screener complete an enrollment for full eligibility and receive instructions on how to accept EA therapy to complete the baseline assessment. Additionally, eligible participants will be randomly assigned to either an experimental group or a control group at 1:1 ratio. Participants then engage with the assigned intervention for 8 weeks following randomization. Participants complete follow-up assessments at baseline, 2, 4, 6, and 8 weeks after randomization, which include the MoCA, Digit Span Test, QoL, and multiple functional assessments. Additionally, participants are prompted to complete ecological momentary assessments [22] twice weekly throughout the 2-month postrandomization period. The study flow diagram is shown in Figure 1.

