### Study Procedures

After screening, eligible participants will be enrolled and they will complete baseline assessments. Thereafter, participants will be randomly assigned to either an EA experimental group or a sham control group. EA or sham treatments will be given twice weekly for 8 weeks—a total of 16 sessions. Participants in both groups will receive routine chemotherapy provided by their oncologists, which will include the use of cytotoxic drugs. Participants will be assessed at the following timepoints (see Figure 2): baseline (T0), midpoint of main treatment (T1-T3) once every 2 weeks, and end of the 8-week main treatment (T4). Assessments include MoCA [24] + Functional Assessment of Cancer Therapy-Cognitive function (FACT-Cog) [25] for cognitive performance, FACT/Functional Assessment of Chronic Illness Therapy-Fatigue (FACIT-Fatigue) [26] for fatigue, European Organization for Research and Treatment of Cancer QoL Questionnaire-Core 30 (EORTC QLQ-C30) [27] for QoL, and Functional Assessment of Anorexia-Cachexia Therapy (FAACT)/FACT-Biologic Response Modifier (FACT-BRM) [28] for chemotherapy-related side effects. Assessments will be done prior to any procedures in that visit, including disease assessment and physician consultation.

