### Statistical Analyses

Cognitive impairment is defined as those with SD>1.5 in the mean scores of MoCA and the QLQ-C30 at baseline for all participants at different timepoints. A time-series test in the Kaplan-Meier survival analysis will be used to compare the incidence of cognitive deficits accumulated after 8 weeks of acupuncture intervention between the 2 groups. Linear mixed-effects modeling will be used to compare participants’ cognitive impairment, fatigue, and depression at baseline, during, and after acupuncture intervention, where only those who have completed at least one assessment at baseline and during treatment will be compared. This model will use time and group as categorical fixed factors and random intercepts and use random intercepts in conjunction with a measurement covariance matrix. Participants’ age, chemotherapeutic drug dosage, fatigue at baseline, depression, and additional treatments will be considered as covariates in the statistical analyses. A 2-sided *t* test will be used to compare the covariates at each timepoint between the 2 groups. The chi-square test will be used for qualitative information and the *t* test will be used for continuous information at baseline. Statistical significance will be considered at *P*<.05. The study data used will be statistically analyzed using SPSS software (IBM Corp) under the supervision of a statistician. To ensure the privacy of the patients, all relevant study data and personal data will be kept in a locked file cabinet. Electronic data will be stored on an encrypted computer and will not be stored on any external storage device. Each participant will be assigned his or her own ID in the study record, which will be used in lieu of his or her name and personal identifying information. Clinical data from the study will be kept in a separate file from the participant’s personal data. The principal investigator will be responsible for all the clinical trial data. During and after the clinical trial, the principal investigator, researchers, and the ethical review committee have the right to view the study data. Participants will have the right to access their personal data and the results of the study. All study data will be stored for a minimum of 3 years after the completion of the trial, after which they will be destroyed in accordance with the rules of the ethics review committee.

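### Patients already on chemotherapy are both admitted and, read literally, excluded, and the article does not settle whether entrants are already impaired although it plans to compare incident impairment

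*Protocol article*

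**What the plan says.** **Chemotherapy status.** In Inclusion and Exclusion Criteria, inclusion (3) takes patients who "are currently undergoing or just about to commence a comprehensive treatment of chemotherapy". Exclusion (1), in the next sentence, removes those who have "undergone chemotherapy within the last 2 years". Study Procedures adds: "Participants in both groups will receive routine chemotherapy provided by their oncologists".

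**Cognitive status at entry.** The Abstract (Methods) states: "We will enroll 168 older patients with cancer with clinically confirmed chemobrain". Study Design states: "Those who report clinically significant cognitive impairment are being recruited and enrolled". Participants and Recruitment lists clinical confirmation as one item of the initial screener. The criteria list itself names no cognitive requirement. For the screener, Study Design says of patients that "they report the levels of cognitive dysfunction they are experiencing through the Overall Anxiety Severity and Impairment Scale", together with the matching depression scale.

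**Aim and endpoint.** The Abstract (Conclusions) and Assessments name prevention as well as relief of symptoms. Sample Size Estimation assumes a 30% incidence following chemotherapy, lowered by 10% to 20% with acupuncture. Statistical Analyses uses a Kaplan-Meier method to "compare the incidence of cognitive deficits accumulated after 8 weeks of acupuncture intervention between the 2 groups", and defines impairment through a 1.5 SD rule on MoCA and QLQ-C30 tied to baseline scores.

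**The concern.** There are two separate conflicts.

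The first is operational. A patient in the middle of a course satisfies inclusion (3) and, on the plain words, also meets exclusion (1). Two screeners could reach opposite decisions on the same patient. Applied literally, the rule leaves only patients about to start who have had no chemotherapy for 2 years, and they can hardly have confirmed impairment from the course under study.

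The second is between population and endpoint. An incidence is defined only in people free of the event at entry. Patients already past the cutoff at baseline are either not at risk or, if left in, count as events that treatment could not have prevented. The 30% planning rate does not describe them. The screening instruments do not resolve this, because they are named as anxiety and depression scales and so do not establish cognitive status.

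**Working it through.** **Step 1. Eligibility, by reading.** Inclusion (3) offers two routes: on chemotherapy now, or about to start. Exclusion (1) carries no carve-out for the current course, so its literal reach covers the whole first route. The Abstract (Conclusions), Introduction and Study Design all say that on-treatment patients are wanted.

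**Step 2. Population against endpoint, by reading.** The Abstract (Methods), Study Design and Participants and Recruitment point to impairment at entry. The criteria list is silent. The prevention aim, the 30% incidence and the Kaplan-Meier comparison point to freedom from impairment at entry.

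**Step 3. The stated sample size.** The article gives 84 per group including 20% dropout. From its stated inputs (30% versus 10%, two-sided 5%, 80% power) the pooled two-proportion formula gives 62 per group, or 78 after dividing by 0.8, so 84 is not reproduced. That is a separate matter. Here I take 84 as given: 84 × 0.8 = 67.2, so about 67 evaluable per arm.

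**Step 4. Share past the cutoff at baseline.** The article gives no figure. The wording of the impairment definition is loose; its evident reading is 1.5 SD on the worse side of the cohort's own baseline mean.
- If scores are normal: Φ(−1.5) = 0.067.
- For any distribution, one scale, one side: at most 1/(1 + 1.5²) = 1/3.25 = 0.308.

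The bound also holds if both scales must cross. A rule met by either scale would loosen it, and the text does not say which is meant.

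**Step 5. Power among those at risk.** Let n = 67 × (1 − share). Power = Φ{[d√n − 1.96√(2p̄(1 − p̄))] / √[p1(1 − p1) + p2(1 − p2)]}. With p1 = 0.30 and p2 = 0.10: d = 0.20, p̄ = 0.20, √0.32 = 0.566 and √0.30 = 0.548.

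| Share past cutoff | n per arm | Standardised value | Power |
|---|---|---|---|
| 0 | 67.0 | (1.637 − 1.109)/0.548 = 0.965 | 83% |
| 0.067 | 62.5 | (1.581 − 1.109)/0.548 = 0.863 | 81% |
| 0.308 | 46.4 | (1.362 − 1.109)/0.548 = 0.463 | 68% |

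These use the favourable end of the assumed reduction, read as absolute. For 30% versus 20%, the same shares give 27%, 25% and 20%; power there is already low with nobody impaired at entry.

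**Step 6. If baseline cases are left in as events.** Assume the same share s in both arms, all counted as events, so that each arm's rate becomes s + (1 − s)p with n = 67.
- s = 0.067: 0.067 + 0.933 × 0.30 = 0.347 and 0.067 + 0.933 × 0.10 = 0.160; power about 70%.
- s = 0.308: 0.308 + 0.692 × 0.30 = 0.515 and 0.308 + 0.692 × 0.10 = 0.377; power about 36%.

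This compares proportions at 8 weeks and only approximates the Kaplan-Meier comparison. It shows that excluding baseline cases costs less power than counting them.

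**The case against.** The case for leaving this alone has four parts.

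- **Exclusion (1) was probably meant for an earlier course.** The past tense, and the fact that both groups receive chemotherapy, favour that reading. This stands as to intent. It makes the defect one of drafting that a few words cure, but the words are not there.
- **Screening has two stages.** Confirmation of chemobrain is checked at the screener, and full eligibility follows. This explains how a cognitive requirement could operate outside the list. It does not remove the conflict, because a cohort selected for impairment fits the incidence plan even less well.
- **The event is a score cutoff, not clinical chemobrain.** This stands on the evident reading of Statistical Analyses, and it is why the loss of power is modest once baseline cases are set aside.
- **The main outcome is largely unaffected.** The Abstract (Results) and Introduction already name the MoCA score or its change as primary, and a mixed model over time is planned. A continuous outcome works in a mixed population. This also stands.

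A reader might go further and infer that current chemotherapy is both required and forbidden, that none of the 168 patients can be at risk, or that the trial cannot say whether it tests prevention or treatment. The article does not support these. Current chemotherapy is one of two admissible routes. A cutoff relative to the cohort's own baseline leaves most patients event-free even if all have clinical chemobrain. Both aims are stated.

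**Conclusion.** The point holds in a limited form. The overlap between inclusion (3) and exclusion (1) is a real contradiction in the printed criteria and affects who is enrolled, which an analysis plan cannot repair. The conflict between the described entrants and the incidence comparison is also real.

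Its size depends on what counts as an event. Under the 1.5 SD reading, with 67 evaluable per arm, 30% versus 10% and a two-sided 5% test, power among those at risk falls from 83% to about 81% if scores are normal, and to about 68% at the single-scale bound. These are losses for the incidence analysis only. If clinical chemobrain itself is the event and every entrant has it, that comparison has no at-risk group. The baseline share is an assumption throughout.

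**What to change.** 1. State in Inclusion and Exclusion Criteria whether exclusion (1) covers the current course, so that it agrees with inclusion (3). Which rule applies is for the sponsor to decide.
2. Reconcile the Abstract, Study Design, Participants and Recruitment, and the criteria list on whether impairment is required at entry.
3. Classify cognitive status at entry with the MoCA already collected at T0, not with the anxiety and depression scales.
4. Restrict the Kaplan-Meier incidence analysis to patients not past the impairment cutoff at baseline. Status is fixed before randomisation, so the comparison within this subset remains randomised.
5. Keep the MoCA score, already named as primary, as the main comparison, analysed with baseline adjustment in all randomised patients.

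**Cost.** A protocol clarification or amendment and matching analysis wording, with no new data collection. The incidence analysis uses fewer patients. The 11 participants recruited by October 21, 2023, and any since, must be checked against the reconciled criteria.
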